## Abstract

**Background:**

Nocturia is a common and bothersome symptom in the elderly population, significantly impacting their quality of sleep and overall well-being. Heat-Sensitive moxibustion (HSM) is effective for elderly people with nocturia, but its efficacy has not been scientifically proven. This randomized controlled trial is designed to determine the efficacy and safety of HSM in the elderly with Nocturia.

**Method:**

This study is designed as a randomized, single-blind clinical trial, focusing on a population of 110 patients aged 60 and above who suffer from non-specific nocturia lasting for at least 1 month. Patients in the intervention arm are scheduled for 2 cycles of HSM, while patients in the control group will undergo the same cycle of conventional treatment. To ensure objectivity, assessors and investigators will remain blinded to the randomization process. The primary outcome of this study is the reduction in the frequency of nocturia. Additionally, several secondary outcomes will be evaluated, including sleep quality, quality of life scores, the efficacy of traditional Chinese medicine (TCM) syndrome, and changes in blood biomarkers Arginine vasopressin (AVP) and Atrial natriuretic peptide (ANP). These assessments will be conducted at baseline, post-intervention and at the 2-month follow-up to comprehensively evaluate the effectiveness and safety of HSM.

**Discussion:**

In this study, we aim to quantitatively analyse the therapeutic effect and safety of HSM on nocturia in the elderly, clarify the amount of moxibustion, the distribution pattern of heat-sensitized acupoints, the frequency of heat-sensitized acupoints, and the moxibustion sensation for the treatment of senile nocturia, which can bring insights into future clinical treatments.

## 1 Introduction

Nocturia is a condition where an individual experiences the necessity to awaken at least twice during the night for the purpose of urination, which is associated with a multitude of adverse health sequelae, including the exacerbation of sleep disturbances, the induction of depressive states, and a concomitant deterioration in the quality of life (1). The prevalence of nocturia was ranging from 11% to 44% among populations aged 20–40 years, while 28%–62% of the elderly (> 70 years old) voiding two or more times per night (2). Recent studies have shown that as the frequency of nocturia increases, mortality increases in a frequency-dependent manner, which may be related to impairment of physiological nocturnal blood pressure drop, increased sympathetic nerve activity, and insulin resistance (3, 4). However, this symptom has not garnered the attention it deserves until now. It was reported that 50 million people are affected by this disorder in the US, but only 1.5 million receive treatment (5). The pathophysiology of nocturia is complex and multifactorial, and may originate from the urological system (lower tract symptoms) or non-urological system, including chronic heart failure, hypertension, diabetes, sleep disorders, etc. Nocturia is characterized by disrupted circadian regulation of fluid homeostasis, and two key hormonal pathways were prioritized based on their mechanistic relevance. Current research has found that arginine vasopressin (AVP) and the water homeostasis biological system are closely related to the occurrence of nocturia. AVP is the primary hormone regulating water homeostasis, promoting renal water retention through increased osmotic driving force and transcellular water transport in epithelial cells (mediated by the cGMP-PKG signaling pathway and AQP2-binding proteins), ultimately enhancing urine concentration (6). Consequently, a deficiency in AVP leads to decreased blood osmolality and subsequent increase in water excretion, resulting in clinical manifestations such as polyuria and nocturia. Another class of hormones involved in water salt balance, the diuretic peptide family, may also play a role. Atrial natriuretic peptide is secreted by the right atrium under the stimulation of atrial wall expansion and is sensed by atrial volume receptors, accounting for the majority of the total amount of diuretic peptides in the circulation (7). A multicenter retrospective cohort study in Japan showed that patients with nocturia had elevated ANP levels, and even higher ANP levels in urine (8). The management strategy of nocturia encompasses a multidisciplinary approach, including pharmacological interventions, notably desmopressin, diuretics, antimuscarinics, and non-steroidal anti-inflammatory drugs (NSAIDs), physical therapy and regular follow-ups (9). In patients receiving desmopressin for the treatment of nocturia, the incidence of hyponatremia is 4.4%, influenced by factors such as age, comorbidities, concurrent medications, and reduced estimated glomerular filtration rate (eGFR) levels (10). Clinicians should implement routine monitoring protocols, including serum sodium checks, particularly in high-risk populations to ensure the safe and effective use of desmopressin (11). While these interventions exhibit certain therapeutic benefits, their limitations such as poor specificity, pronounced side effects, protracted treatment durations, and substantial costs often yield outcomes that fall short of expectations (12). Hence, the development of novel and alternative medical management strategies for nocturia remains a challenging task and is urgently required.

Heat-sensitive moxibustion is a moxibustion therapy focused on the “heat sensitivity” of acupoints and the qi-obtaining effect of moxibustion (13), with the advantage of featuring simplicity, safety, effectiveness, and non-toxic side effects (14). When performing moxibustion over traditional meridians and acupoints, if a distinct area experiences one or more phenomena of heat penetration, heat transfer, or thermal conductivity, that specific location can be precisely identified as the heat-sensitive acupoint. In contrast to mild moxibustion, applying specific techniques to stimulate the qi-obtaining effect of moxibustion and achieving individualized desensitization moxibustion at heat-sensitive acupoints can significantly improve the therapeutic effect (15). A randomized controlled trial demonstrated that HSM achieved a total effective rate of 92.0% in migraine treatment, significantly superior to the 72.0% efficacy observed with mild moxibustion (16). Researchers have verified that the thresholds pertaining to heat perception, heat-induced pain, and heat pain tolerance are markedly elevated at heat-sensitive acupoints in comparison to non-heat-sensitive counterparts by using quantitative temperature sensation assessment techniques, thereby furnishing robust support for the genuine presence of the heat-sensitive state within acupoints (17). Over the past years, HSM has gained extensive application in treating a range of conditions affecting the cardiovascular, digestive, nervous, sports systems and so on (18). Meanwhile, limited trials had revealed that HSM can significantly reduce the frequency of nocturia, the degree of urinary frequency, and improve the quality of life and sleep in patients with nocturia, making it an effective treatment for nocturia that is worthy of clinical promotion and application (19). The mechanism of HSM in treating diseases exhibits a multi-target, multi-dimensional, and multi-pathway approach, primarily involving inflammatory response, immune regulation, cell proliferation and apoptosis, as well as hormonal balance within the body (20). The integrative effect of multiple brain regions showing significant changes aligns with the somatic pain-temperature conduction pathway following HSM, suggesting that somatosensory system activation may serve as the neurobiological foundation for meridian sensation transmission, while the coordinated network of these regions mediates HSM’s therapeutic effects through ACC-IC medial pain system modulation of emotional network integration (21). Mechanistically, HMS may normalize circadian hormone secretion through central neural activity. Despite the promising potential of HSM for the elderly with nocturia, there is a notable paucity of clinical randomized controlled trials (RCTs) with high qualified evidence in the literature to date.

Thus, further extensive and rigorous RCTs are warranted to comprehensively assess the safety, efficacy, and applicability of this therapeutic approach in elderly patients, which not only could advance our understanding of the mechanism and outcomes of heat-sensitive moxibustion but also provide the necessary scientific evidence to support its clinical application for the management of senile nocturia.

## 2 Methods

### 2.1 Trial design

The trial utilizes a prospective, randomized and single-blind design. A flow diagram of the study design is shown in Figure 1, and the study schedule is depicted in Table 1.

**FIGURE 1 F1:**
[figure not shown]
The flow chart of the clinical procedures.

**TABLE 1 T1:** Schedule of enrollment, intervention and assessment.

Time point	Enrollment Week -1	Allocation Week 0	Treatment phase Week 1-2	Follow-up Week 3	Follow-up Week 10
**Assessment of eligibility**					
Eligible screen	X	–	–	–	–
Informed consent	X	–	–	–	–
**Randomization**					
Allocation	–	X	–	–	–
**Intervention**					
Conventional treatment	–	–	X	–	–
Heat-sensitive moxibustion plus conventional treatment	–	–	X	–	–
**Primary outcome**					
The frequency of nocturia	–	X	–	X	X
**Secondary outcomes**					
Pittsburgh sleepiness index (PSQI) scale	–	X	–	X	X
Nocturia on quality of life (N-QOL) questionnaire	–	X	–	X	X
Traditional Chinese medicine syndrome scoring scale	–	X	–	X	X
The level of arginine vasopressin (AVP)	–	X	–	X	X
The level of atrial natriuretic peptide (ANP)	–	X	–	X	X

### 2.2 Study setting

The project department is the Comprehensive Third Department at Guangdong Provincial Hospital of Traditional Chinese Medicine, which has a wide range of case sources, ensuring the availability of case data for this project. This prospective clinical trial will be conducted between January 1, 2024 and December 31, 2025.

### 2.3 Research hypothesis

Primary hypothesis: HSM groups will experience significant improvement in the frequency of nocturia.

Secondary hypothesis: HSM groups are anticipated to exhibit notable enhancements in sleep quality, quality of life, as well as traditional Chinese medicine (TCM) syndrome scores.

### 2.4 Study participants

#### 2.4.1 Inclusion criteria

① Complied with the Western medical diagnostic criteria “an individual wakes up one or more times during the night to void with each void preceded and followed by sleep or the intention to sleep,” combined with at least one diagnosed pathology, including benign prostatic hyperplasia and overactive bladder (22) and complied with the traditional Chinese medicine kidney yang deficiency syndrome diagnostic criteria for nocturia (The second edition of Differential Diagnosis of Traditional Chinese Medicine Syndromes); ② Patients aged ≥ 60 years, regardless of gender; ③ The patient’s duration of illness is 1 month at least; ④ Normal urine routine test results and negative urine bacterial culture; ⑤ Patients with a sense of urination and the ability to control urination; ⑥ Patients with clear consciousness, rational mentality, cooperative behavior, articulate speech, who could accurately express their own wishes and communicate their moxibustion experience correctly with the practitioner; ⑦ Patients who are willing to participate in the study and have signed the informed consent form.

#### 2.4.2 Exclusion criteria

① Individuals who experience dizziness during moxibustion or have allergies or intolerance to mugwort smoke; ② Patients with large areas of skin lesions, ulcers, or sensory impairment at the moxibustion site; ③ Patients with urinary tract infections evidenced by positive urine routine tests or urine bacterial cultures, accompanied by or without symptoms such as urgency and pain during urination; ④ Patients diagnosed with stress incontinence, urge incontinence, mixed incontinence, overflow incontinence, or individuals requiring indwelling urinary catheterization; ⑤ Patients with urinary system organic diseases such as nephritis, renal cell carcinoma, ureteral stones, and bladder cancer; ⑥ Patients with severe primary diseases in the cardiovascular, cerebrovascular, liver, kidney, hematopoietic, or endocrine systems, as well as those with intellectual disabilities; ⑦ Patients who have undergone surgery, have tumors, or have unstable blood pressure or blood sugar levels; ⑧ Critically ill patients, those with severe mental illnesses, or those with communication barriers such as speech difficulties; ⑨ Patients who have taken medications that could interfere with this study within the last week, such as diuretics, or are currently receiving medication or non-pharmacological treatments for nocturia; ⑩ Patients who are currently participating in clinical trials for other medications or treatments and withdraw from the study voluntarily or are lost to follow-up.

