### 2.12 Data collection and analysis

The data of various observation indicators of patients were collected on the day of treatment, the day after the end of treatment and 2 months after the end of treatment. To ensure the accuracy and completeness of the data, we will adopt a double-entry method. PASW Statistics 18.0 software was used to establish a database for case investigation data that met the inclusion criteria, and data review was performed after data entry was completed.

The statistical analysis of the PASW Statistics 18.0 data was performed, encompassing descriptive statistics for clinical baseline data. For continuous outcomes, group differences will be analyzed using Student’s *t*-tests if data are normally distributed; otherwise, the Mann-Whitney U test will be applied. For categorical variables, Chi-square tests or Fisher’s exact tests will be used as appropriate. Efficacy evaluations utilized both intention-to-treat (ITT) and per-protocol (PP) populations, while safety assessments were conducted on the safety analysis set. In the intention-to-treat analysis, missing data due to withdrawal or dropout will be handled using the last observation carried forward (LOCF) method. Participants who received prohibited therapies were retained in the trial per the ITT principle but flagged for sensitivity analysis. Their data were analyzed both within the full cohort and in a subgroup excluding protocol violators. When necessary, multiple imputation methods will be considered for missing value replacement, or alternative approaches will be selected based on actual circumstances. For clustering, the K-MEANS clustering method was utilized, while applying Pearson or Spearman correlation analysis to examine correlations. A *P*-value of 0.05 or less was considered statistically significant.

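### Exclusion criterion 10 excludes participants for withdrawal or loss to follow-up, contradicting the plan's own intention-to-treat rule and dropout allowance

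*Protocol article*

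**What the plan says.** Section 2.4.2 of the Protocol article lists ten exclusion criteria. The tenth begins with people who are taking part in other trials and then, joined by an 'and', adds those who "withdraw from the study voluntarily or are lost to follow-up". The first criterion reads "Individuals who experience dizziness during moxibustion or have allergies or intolerance to mugwort smoke".

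Section 2.12 sets out the analysis: "Efficacy evaluations utilized both intention-to-treat (ITT) and per-protocol (PP) populations", and "safety assessments were conducted on the safety analysis set". For the ITT analysis, "missing data due to withdrawal or dropout will be handled using the last observation carried forward (LOCF) method". Protocol deviators are also kept: "Participants who received prohibited therapies were retained in the trial per the ITT principle but flagged for sensitivity analysis".

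Section 2.9 raises the sample size to 110 (55 per group) to allow for at most 15% dropout. Table 1 places eligibility screening in Week -1 and allocation in Week 0. Section 2.8.3 requires all adverse events to be observed and reported.

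**The concern.** An exclusion criterion decides who may enter the trial and has to be answerable at screening. Withdrawal and loss to follow-up are not. They arise after enrolment and, apart from a person who withdraws between consent and allocation, after randomisation. Listing them as exclusions lets a randomised participant be declared ineligible because of what happened later.

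What is at stake is membership of the main efficacy set. Someone who removes leavers can cite section 2.4.2; someone who keeps them can cite section 2.12. Participants know their allocation (section 2.11) and the primary outcome is a urination diary (section 2.8.1), so leaving may depend on both arm and response. Dropping leavers would then compare groups that randomisation no longer makes comparable, under an ITT label.

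**Working it through.** **1. The plan's own figures.** Inputs from section 2.9: Z = 1.96, P = 0.5, E = 10%, dropout at most 15%.

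- Preliminary size: Z² × P × (1 − P) / E² = 3.8416 × 0.25 / 0.01 = 96.04, so 96. This reproduces.
- With dropout: 96 × 1.15 = 110.4, so 110. This reproduces.
- Participants concerned: 110 × 0.15 = 16.5 overall, about 16; per arm 55 × 0.15 = 8.25, about 8.

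These figures do not decide the point. They show that the plan expects leavers and counts them among those enrolled.

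**2. The rules side by side for one person**, randomised and lost before the 2-month visit.

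| Source | Status of this person |
|---|---|
| Section 2.4.2, criterion 10 | Excluded |
| Section 2.9 | Part of the 110, within the 15% allowance |
| Section 2.12, ITT rule | In the analysis, last observation carried forward |

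The first row cannot be reconciled with the other two.

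**3. What applying criterion 10 would do.** The document gives no dropout by arm and no outcome for leavers, so this is an illustration under assumptions. Let completers in both arms improve by 1 unit and leavers by 0. Let dH and dC be the dropout fractions in the heat-sensitive moxibustion (HSM) and control arms.

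- Everyone kept: difference = (1 − dH) − (1 − dC) = dC − dH.
- Leavers removed: difference = 1 − 1 = 0.
- Shift caused by removal = 0 − (dC − dH) = dH − dC.

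| dH | dC | Shift in HSM minus control |
|---|---|---|
| 5%, 10% or 15% | the same | 0.00 |
| 15% | 5% | +0.10 |
| 5% | 15% | −0.10 |
| 15% | 0% | +0.15 |
| 0% | 15% | −0.15 |

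The shift is in units of the completers' improvement. It depends on the imbalance in dropout and can go either way. The zero in the first row also depends on leavers differing from completers by the same amount in both arms.

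**4. The dizziness item.** Criterion 1 is in the present tense and does not say that the reaction must be known beforehand. It sits beside allergy and smoke intolerance, in a list that Table 1 applies at Week -1. The natural reading is a known prior reaction, which is a valid screening item.

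**The case against.** The strongest defence is that section 2.12 is the specific text on analysis and is clear: ITT and per-protocol populations, leavers carried forward, deviators retained. Section 2.9 agrees with it. The clause in criterion 10 is grammatically garbled and looks like a discontinuation or per-protocol rule put in the wrong list. This stands to the extent that removal of leavers is a risk created by conflicting text, not a settled analysis rule. It does not remove the conflict. Reading the 'and' as limiting the clause to people in other trials does not help either, since it makes little sense as an eligibility rule and still rests on a later event.

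Three stronger readings are tempting and not supported:

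- **That the removals would fall mainly in the HSM arm and flatter it.** Criterion 10 applies to both arms and no dropout by arm is given. Unblinded controls, who receive only health education and exercises, could leave as often or more often.
- **That criterion 1 removes a harm from the HSM arm.** Only that arm receives moxibustion, so an on-treatment reading would be one-sided. But a prior reaction is the natural reading, section 2.8.3 still requires every adverse event to be reported, and nothing says that a dizzy participant leaves the safety set.
- **That section 2.12 itself filters out leavers** because the database is set up for "case investigation data that met the inclusion criteria". That sentence refers to the inclusion criteria, not to the exclusion list that holds criterion 10.

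**Conclusion.** The contradiction is real and lies in the text shown: criterion 10 excludes people whom sections 2.9 and 2.12 count and analyse. At the planned ceiling it concerns about 16 of 110 participants. If the criterion were applied, the ITT analysis would become a completer analysis.

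The resulting bias cannot be given a sign or a firm size. The range of −0.15 to +0.15 of the completers' improvement rests on dropout of at most 15% in either arm, equal improvement among completers, and none among leavers. The document states none of these assumptions except the 15% allowance, and it states that only for the trial as a whole.

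The wording of criterion 1 is a matter for clarification and not a demonstrated post-randomisation exclusion.

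**What to change.** - Limit criterion 10 to current participation in another trial. Delete the clause on withdrawal and loss to follow-up, and describe both under discontinuation.
- State in section 2.12 that everyone randomised stays in the ITT set in the allocated group, and that everyone treated stays in the safety set.
- As a clarification only, word criterion 1 so that dizziness or smoke intolerance means a reaction known before randomisation. Say that dizziness arising on treatment is reported as an adverse event, in line with section 2.8.3.

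The cost is a few sentences. No extra participants, visits or measurements are needed. If recruitment has started, the change should be made and dated before the analysis sets are fixed, and anyone already removed under criterion 10 after randomisation should be identified and restored to the ITT set.

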### 2.5 Intervention

#### 2.5.1 Control group: conventional treatment

Based on the Chinese Expert Consensus on Clinical Diagnosis and Treatment of Nocturia published in the Chinese Journal of Urology in 2018, a health education program is designed for research subjects who meet the inclusion criteria, focusing on daily lifestyle habits and exercise routines. The program requires daily implementation by the research subjects.

(1) Restrict fluid intake before bedtime, especially alcohol and coffee and empty the bladder as much as possible before going to bed to improve sleep quality.

(2) Maintain warmth during the night to increase skin blood supply and reduce urine production.

(3) Engage in moderate exercise and elevate the lower limbs to reduce water retention.

(4) For patients with Overactive Bladder (OAB), perform bladder function exercises such as delayed urination.

(5) Conduct pelvic floor muscle exercises.

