#### 2.5.2 Experimental group: heat-sensitive moxibustion plus conventional treatment

(1) Acupoint Selection: Qihai, Guanyuan, Ciliao (bilateral), Yongquan (bilateral).

(2) Acupoint Location: Refer to the national standard of the People’s Republic of China, “Names and Locations of Acupoints” (GB/T123456-2006).

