### 2.10 Randomization and allocation concealment

A third party other than the researchers and evaluators uses a software package to generate random numbers and groups, and compiles and keeps random allocation cards, which are placed in sealed opaque envelopes in sequence. Qualified subjects open the random envelopes with corresponding numbers in the order of inclusion in the trial. In this way, the subjects are randomly divided into the treatment group and the control group, and the operation is carried out strictly according to the grouping in the envelopes.

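### Overactive-bladder status decides part of the background treatment in both arms, but the unadjusted primary comparison does not use it: a modest, avoidable loss of precision, not a bias

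*Protocol article*

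**What the plan says.** **Eligibility (2.4.1).** Patients must meet the nocturia definition "combined with at least one diagnosed pathology, including benign prostatic hyperplasia and overactive bladder". Several diagnoses are therefore mixed, and the diagnosis is known before randomisation.

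**Background treatment (2.5.1).** Conventional treatment is a five-item education programme. Four items carry no diagnostic restriction. Item (4) does: "For patients with Overactive Bladder (OAB), perform bladder function exercises such as delayed urination".

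**Both arms (2.5.2).** The section title reads "Experimental group: heat-sensitive moxibustion plus conventional treatment", and Table 1 agrees. OAB patients in either arm are thus assigned the bladder exercises, and other patients in either arm are not.

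**Allocation (2.10).** A third party "uses a software package to generate random numbers and groups, and compiles and keeps random allocation cards". Envelopes are used by order of inclusion. No stratification factor is mentioned.

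**Analysis (2.12).** "For continuous outcomes, group differences will be analyzed using Student’s" t-tests when data are normal, and by Mann-Whitney U tests otherwise. Neither named test carries a covariate or a stratum. The primary outcome (2.8.1) is nocturia frequency from a 72-hour diary.

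**The concern.** OAB status is recorded at entry, and the plan itself makes treatment content depend on it. It is a natural candidate for a prognostic factor, both because the underlying condition differs and because one group is assigned an additional exercise.

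If OAB patients change by a different amount from the others, an unadjusted two-group test has two costs. The difference between diagnoses stays in the error term, which widens the interval for the HSM effect. In addition, if one arm happens to contain more OAB patients, the observed HSM-minus-control difference moves by the imbalance times the OAB difference, and nothing in the analysis takes that out. In a trial of 110, precision that costs no extra patients is worth having.

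**Working it through.** **The plan's own figure.** Section 2.9 gives Z = 1.96, P = 0.5 and E = 10%. The precision formula for one proportion gives 1.96² × 0.5 × 0.5 / 0.10² = 96.04, matching the stated 96. For dropout, 96 × 1.15 = 110.4, close to the stated 110 (55 per arm). This formula contains no effect size and no SD, so it offers nothing against which to measure the value of adjustment. The inputs below are assumptions, shown as ranges.

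**Inputs.** From the article: N = 110, 55 per arm, 96 (48 per arm) before the dropout allowance, two-sided α = 0.05, power 0.90. Assumed: OAB share p = 20-50%; OAB minus non-OAB outcome difference g = 0.2-0.8 within-diagnosis SDs; simple 1:1 allocation without stratification.

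**Step 1: chance imbalance.** With K OAB patients among 110, the number in one arm is hypergeometric with variance 55 × p(1−p) × 55/109. The SD of the between-arm difference in OAB share is twice the root of that variance, divided by 55.

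| p | SD of difference | P(≥10 points) | P(≥20 points) |
|---|---|---|---|
| 20% | 7.7 points | 0.233 | 0.008 |
| 30% | 8.8 points | 0.212 | 0.037 |
| 50% | 9.6 points | 0.252 | 0.056 |

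**Step 2: shift and power.** The shift in the estimate is g × imbalance. The standard error with 48 per arm is √(2/48) = 0.204 SD. With v = g²p(1−p), diagnosis explains R² = v/(1+v) of the outcome variance. Take an effect with 90% unadjusted power, (1.960 + 1.282) × √(2/48) = 0.66 SD. Adjusted power is then Φ(3.242 × √(1+v) − 1.960), and the gain is worth 96 × R² patients. Ranges run over p = 20-50%.

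| g | Shift at 10 points | Shift at 20 points | R² | Adjusted power | Worth, of 96 |
|---|---|---|---|---|---|
| 0.2 | 0.02 | 0.04 | 0.006-0.010 | 90.2-90.3% | 0.6-1.0 |
| 0.5 | 0.05 | 0.10 | 0.038-0.059 | 91.1-91.6% | 3.7-5.6 |
| 0.8 | 0.08 | 0.16 | 0.093-0.138 | 92.6-93.7% | 8.9-13.2 |

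Beyond the assumed range, g = 1.0 gives 93.7-95.2% power and a 20-point shift of 0.20 SD, about one standard error.

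**Step 3: validity.** In 20,000 simulated unstratified trials with no HSM effect (55 per arm, p = 30%, g = 0.8), the unadjusted t-test rejected in 4.9%. Its overall error rate is intact.

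**Step 4: the single allocation that occurs.** Overall validity averages over balanced and unbalanced allocations. Take a 15-point imbalance, p = 50%, g = 1.0 and 55 per arm. The test uses a standard error of √1.25 × √(2/55) = 0.213, so it rejects beyond ±0.418. Given the imbalance, the estimate is centred at 0.15 with SD √(2/55) = 0.191. The tails beyond (0.418 − 0.15)/0.191 and (0.418 + 0.15)/0.191 sum to about 8%. With g = 0.3 the same steps give about 5.4%. These are normal approximations. Allocations with little imbalance fall below 5%, which is how the average stays at 5%.

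**The case against.** The strongest case against is that nothing here is wrong. Item (4) follows one rule in both arms, so the randomised contrast is HSM or no HSM on a common background. A background rule keyed to a baseline characteristic does not confound that contrast. An unadjusted test in a 1:1 trial is legitimate, and the gain from adjustment rests wholly on assumed inputs. Item (4) is one of five, pelvic floor exercise is offered regardless of diagnosis, and the exclusion of urge and mixed incontinence (2.4.2) may lower the OAB share. All of this stands, and it limits the point to precision.

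Three stronger readings are tempting, and the documents support none of them.

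- A reader might infer that the OAB-only exercise biases the HSM effect. It does not. A chance imbalance has mean zero over randomisations and is covered by the standard error (Step 3).
- A reader might infer that allocation is unrestricted. Section 2.10 mentions no stratification, but a condensed article may leave that to the full protocol. The firm ground is 2.12, which states its tests outright. If allocation were in fact stratified by diagnosis, the stratum would still belong in the analysis.
- A reader might infer that results split by OAB status would show whether HSM adds to bladder exercises. At p = 30% there are about 16.5 OAB patients per arm, and a 95% interval is about ±1.96 × √(2/16.5) = ±0.68 SD. At p = 50% (27.5 per arm) it is about ±0.53 SD. Both are too wide to answer that question.

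**Conclusion.** The point holds as a modest recommendation on precision. The plan has a baseline factor that sets background treatment, already knows it for every participant, and names a primary comparison that cannot use it. The comparison is valid and unbiased as written.

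Under the assumed ranges, a 10-point or larger imbalance in OAB share arises in about 21-25% of allocations and one of 20 points or more in about 1-6%. At 10 or 20 points the estimate moves by 0.02-0.16 SD, less than one standard error. Adjustment raises 90% power by roughly 0 to 4 percentage points. The gain is close to nil if OAB status barely predicts the outcome. It may also be smaller than shown once the baseline count is in the model, because the two can overlap. The article gives no figure that would narrow these ranges.

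**What to change.** In 2.12, replace the unadjusted primary comparison with a pre-specified linear model (ANCOVA) for nocturia frequency. Its terms should be treatment arm, the baseline nocturia count and OAB status at entry (yes/no), with the adjusted HSM-minus-control difference and its 95% interval as the primary result. If the data are non-normal, use a rank test stratified by OAB status in place of the plain Mann-Whitney U test. Fix this before unblinding. Any results by OAB status should be labelled descriptive, with no subgroup claim.

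The OAB term costs one degree of freedom, and the change replaces the named primary method. That is more than adding a term, since a t-test or Mann-Whitney U test cannot take a covariate. No new data are needed, because diagnosis is established for eligibility and the baseline count is already scheduled in Table 1. Leave the allocation procedure as it is. The trial is scheduled from January 2024 to December 2025, and splitting envelopes by diagnosis partway through would alter the randomisation for little gain.
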